#### Outcome measures

2.3.5

Participant's self-rating.1.Level of illness-related disability

Functional impairment is measured by the 36-item interview version of the World Health Organization Disability Assessment Schedule 2.0 (WHODAS 2.0). This measure assesses respondent functioning in six domains: Cognition (six items), Mobility (five items), Self-care (four items), Getting along with people (five items), Life activities (four items), Household (four items) and Participation (eight items). WHODAS 2.0 has demonstrated reliability, validity and sensitivity to change in samples with psychotic illnesses as well as a wide variety of both psychiatric and non-psychiatric illnesses [23,24]. In the Swedish context, a previous study with post-stroke patients has shown high levels of overall internal consistency and moderate to high levels of internal consistency on five of the six subscales, with “Getting along with people” being the one subscale showing non-satisfactory consistency [25]. The interview administered WHODAS 2.0 at treatment completion is one of the studies two primary outcome measures.2.Illness management skill and sense of recovery

To assess participants' illness management skills and sense of subjective recovery the self-respondent version of the Illness Management and Recovery Scale (IMRs) will be used. This is an instrument specifically designed to assess successful treatment outcome in patients participating in IMR. It consists of 15 items, scored on five-point scale. The items generate a total score and scores on three subscales, illness management ability, sense of recovery and substance use [26]. The Swedish version of the scale has demonstrated satisfactory internal reliability, strong test-retest reliability and convergent validity with other measures of symptoms, sense of recovery and quality of life, in a sample of Swedish respondents suffering from schizophrenia or schizoaffective disorder [10].3.Hope

To assess participants' levels of hope the Adult State Hope Scale (ASHS) will be used. This is a self-rating scale constructed to measure a respondent's level of hope by six items, answered on an eight-point scale [27]. This measure has been used in previous studies of IMR, and positive effects of the treatment have been demonstrated [28]. A previous study also demonstrated a correlation between the activity levels of schizophrenic patients participating in IMR and the ASHS [29].  

Clinician's rating.1.Mental health and security related problems

To assess the participant's mental health and the extent of security related problems affecting them, the Health of the Nation Outcome Scale-Secure version (HoNOS-S) [30,31] will be used. This is a questionnaire consisting of 19 items rated by a clinician on a five-point scale. Twelve clinical items assess the extent of the patient problems in four areas: behavior, function, symptoms and social adaption. In addition to the twelve clinical items in the original version, the secure version of HoNOS [31] also contain seven items that focus on the need for special security measures in conjunction with the care provided for the patient rated. In this project, the participants treating psychiatrists will be asked to answer this questionnaire. The HoNOS-S administered at treatment completion is the second primary outcome measure in the study.2.Level of illness-related disability

In addition to the interview version of WHODAS 2.0, the 36-item proxy-administered version of WHODAS 2.0 will be used. In this version an informant with good knowledge of the person assessed is asked to answer the same questions posed in the interview version of WHODAS 2.0, with necessary revisions to wording made to adapt it to the third person perspective of the proxy respondent [23]. This scale will be answered by a member of the forensic mental health staff with good knowledge of the participant.3.Illness management skill and sense of recovery

Similar to WHODAS, IMRs also exist in a proxy-answered version. This version of the scale consists of the same number of items (15) answered on the same five-point scale as the self-report version of the questionnaire [26]. The same proxy-respondent answering WHODAS will be asked to answer the proxy-version of IMRs.

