Treatment is planned to take place during two group meetings and one individual follow-up meeting per week. Group meetings will be used to discuss and work with new treatment material, share experiences amongst group members, monitor progress towards subjectively meaningful recovery goals and set homework assignments for the next group session. Individual sessions will be used to repeat and clarify information given at group sessions, tailor homework to the individual patient, support completion of homework and efforts towards achieving recovery goals. The IMR material does not state a set number of sessions for the treatment, instead the material is worked through in a pace adapted to the patients receiving treatment. However, based on our experience we estimate that the active treatment phase will last for approximately nine months. Treatment sessions will be led by the forensic mental health staff at the wards participating in the active condition (i.e. psychiatric nurses and auxiliary psychiatric care-givers). Staff administering IMR-treatment will receive two full days of training in the method, as well as a weekly supervision session during the treatment period. Training in IMR will consist of lecture style presentation of information about treatment goals and contents as well as practical exercises in using methods included in the treatment material. During training sessions, participating personnel will also be encouraged to discuss how IMR can be optimally integrated in the daily routine of clinical work. The supervision sessions will consist of 1 h weekly meetings in a group setting, focusing on solving problems emerging in treatment as well as rehearsing and emphasizing treatment goals. This training and supervision will be provided by members of the research team, mainly KS and PA. During the treatment phase, responsibility for practically leading and implementing IMR will be the staff leading and planning daily work at the ward in question (i.e. the person or persons holding leadership positions at the ward participating in the treatment condition). The caseload of individual treatment providers could vary somewhat depending on variability in staffing and local decisions regarding the division of tasks at individual treatment sites. Based on the length of the IMR-program and estimations of staffing at an inpatient facility, we estimate that the mean number of group and individual session provided by individual staff at wards in the active condition will be approximately 5 and 10, respectively. The IMR treatment integrity scale (IT-IS) [17] will be used to assess treatment fidelity in the active condition, which is described in further detail below.

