Firstly, there are differences between how countries structure forensic mental health care and how mental illness is considered in different judicial systems. Thus, when considering the generalizability of the results of our study to another national context, differences in national jurisprudence and practice of forensic mental health delivery should be taken into account. Secondly, the practitioners delivering IMR in our study will, as mentioned, be forensic mental health nurses and auxiliary staff at the wards in our active condition. They may have limited previous experiences with delivering structured psychosocial interventions. Thus, it is plausible that better quality of treatment could be insured by assigning treatment delivery to staff with more experiences of group treatments, e.g. a licensed psychologist well versed in IMR-treatment. However, previous studies with IMR have employed a similar method of delivery, with regular staff serving as group leaders after receiving training in IMR [11,39,40]. Our experience is that this is the usual mode of delivery for psychosocial interventions when applied within inpatient settings. Thus, we consider this aspect of our design to be a part that strengthens the ecological validity of the study. Furthermore, we have tried to compensate for this potential weakness by providing clinical supervision and by inclusion of process measures within our design.

Lastly, we would have wished to be able to include a larger number of participants within our study, to ensure sufficient statistical power. In planning our study, we have found it necessary to balance a desire for sufficient sample size against practical considerations based on finite resources and environmental constraints. Thus, results from outcome measures will have to be interpreted and reported with caution. However, our proposed sample size is comparable or markedly larger than samples included in several previous studies of IMR [[16], [39], [40]]. It should also be noted that the current project is not solely concerned with treatment outcomes but also pertain to staff experiences of implementing and working with IMR, which can hopefully add to our understanding of interventions of this kind when applied in this context. We also hope that our study can stimulate further enquiry into the effectiveness of psychosocial interventions within the forensic mental health field and ideally support meta-analytical efforts within the area.

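### Section 2.3.5 allows staff who deliver IMR to act as proxy raters (WHODAS and IMRs, both non-primary) for participants they treat, and the plan neither prevents nor records this

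*Protocol article*

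**What the plan says.** Under Outcome measures (section 2.3.5, clinician's rating), the rule for the proxy WHODAS is: "This scale will be answered by a member of the forensic mental health staff with good knowledge of the participant". For the second proxy scale: "The same proxy-respondent answering WHODAS will be asked to answer the proxy-version of IMRs". The note to Table 1 confirms that WHODAS and IMRs are each collected in a client version and a clinician version. Section 2.3.5 also describes the IMRs: "This is an instrument specifically designed to assess successful treatment outcome in patients participating in IMR".

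On delivery, section 2.2.4 says: "Treatment sessions will be led by the forensic mental health staff at the wards participating in the active condition". The Discussion repeats that providers will "be forensic mental health nurses and auxiliary staff at the wards in our active condition". Section 2.2.4 gives the intensity ("Treatment is planned to take place during two group meetings and one individual follow-up meeting per week"), the duration ("we estimate that the active treatment phase will last for approximately nine months") and the expected spread of work: "the mean number of group and individual session provided by individual staff at wards in the active condition will be approximately 5 and 10", group and individual respectively.

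The primary outcomes are the interview WHODAS and the HoNOS-S, both at treatment completion. The treating psychiatrist completes the HoNOS-S.

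**The concern.** Raters and providers come from the same group of people, and the only selection rule is that the rater knows the participant well. Delivering IMR sessions is one way to gain that knowledge. A provider who acts as proxy would score a scale built around the aims of the sessions they lead, after training and weekly supervision in that treatment.

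Control-ward proxies are not stated to be masked either, but they are not rating a trial treatment that they delivered. The plan avoids training staff who regularly work in both arms (section 2.2.6), so the overlap of provider and rater belongs to the active arm. A tendency to rate one's own work favourably would not cancel between arms and would appear as a treatment effect on the proxy scales. Proxy results that agree with self-ratings would then be weaker support than they look. Because the proxy's IMR role is not recorded, the problem could not be examined afterwards.

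**Working it through.** **Text check**

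- Rater pool (2.3.5): forensic mental health staff who know the participant well; one person for both proxy scales.
- Provider pool (2.2.4, Discussion): nurses and auxiliary staff on the active wards.
- Safeguards: section 2.2.6 covers training, use of IMR material on control wards and sharing of information. It does not cover who rates outcomes. The limitations in the Discussion mention providers' inexperience, not providers as raters.

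Overlap is therefore permitted, not required.

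**How widely delivery is spread**

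Inputs: 80 participants on 12 wards (2.2.1); nine months, about 39 weeks; one individual and two group sessions a week; about 10 individual and 5 group sessions per staff member (2.2.4). Assumption: one leader per session.

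- Participants per ward: 80/12 = 6.67.
- Individual sessions per active ward: 39 × 6.67 = 260, so 260/10 = about 26 providers.
- Group sessions, taking one group per ward: 39 × 2 = 78, so 78/5 = about 16 leaders.
- Share of one participant's individual sessions that an average provider could cover: at most 10/39 = about 26%.
- Fewest leaders for one participant's individual sessions: 39/10 = 3.9, about 4, and only if sessions are allocated by participant.

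On these figures many ward staff deliver IMR, so overlap is plausible without any rule. They do not describe one fixed weekly therapist per participant.

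**What a rating shift would do**

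The plan gives no figure to reproduce here. Assumptions: true effect 0, 40 per arm, two-sided 5% test on 10 df (12 wards − 2), average shift b (in SD) across all active-arm proxies, ICC from 0 to 0.10.

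- Design effect = 1 + (6.67 − 1) × ICC; SE(d) = √(2 × design effect / 40).
- Rejection rate = probability that a noncentral t (10 df, noncentrality b/SE) exceeds ±2.228.

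| ICC | Design effect | SE(d) | b = 0.1 | b = 0.15 | b = 0.2 | b = 0.3 |
|---|---|---|---|---|---|---|
| 0 | 1.000 | 0.224 | 6.9% | 9.3% | 12.8% | 22.9% |
| 0.05 | 1.283 | 0.253 | 6.5% | 8.4% | 11.1% | 18.9% |
| 0.10 | 1.567 | 0.280 | 6.2% | 7.8% | 9.9% | 16.3% |

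The shift is an average over all active-arm proxies. If half are providers and each shifts by 0.2 or 0.3 SD, the averages are 0.1 and 0.15 SD. At ICC 0.05 the rates are then 6.5% and 8.4%, not 11.1% and 18.9%.

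**The case against.** The strongest reply is that this reaches only non-primary outcomes. That stands. Table 1 stars the WHODAS row and its note covers both versions, so a reader might infer that a primary outcome is exposed. Section 2.3.5 settles it: the primary is the interview version, and the other primary is rated by the psychiatrist.

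A reader might also infer that the proxy will usually be the participant's regular weekly IMR therapist. The documents do not support this. About 10 individual sessions per staff member over 39 weeks points to shared delivery, and on a long-stay ward good knowledge can come from daily contact.

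Nor do the plan's figures show that barring a participant's session leaders is easy. About 4 of 26 holds only if sessions are allocated by participant. Section 2.2.4 leaves the division of tasks to local decision, and the article gives no ward staffing number. If sessions rotate, many more staff would be excluded. Similarly, dropping every IMR-trained proxy from a sensitivity analysis could empty the active arm while leaving control almost intact. Staff who lead none of a participant's sessions may still be trained providers on the same ward, so separation reduces the stake without removing it.

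Finally, no document gives the size or direction of any shift. What remains is that the article itself fixes the rater rule, that the rule permits the overlap, and that the overlap goes unrecorded. A later analysis plan could not recover information that was never collected.

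**Conclusion.** The point holds in limited form. Section 2.3.5 permits IMR providers to rate participants they treat on the proxy WHODAS and proxy IMRs. This can happen in the active arm only, and the plan neither prevents nor records it. Both primary outcomes are outside its reach.

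The size is illustrative: about 6-23% false positives on a proxy scale instead of 5%, for an average active-arm shift of 0.1 to 0.3 SD. The shift, the ICC range and the 10 df are assumptions. How many proxies would be providers cannot be determined from the documents. The point merits a change because the change is cheap, not because bias has been shown.

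**What to change.** In section 2.3.5:

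1. Name each participant's proxy when eligible patients are identified, before the ward is randomised (that step already exists in section 2.2.1). Keep the same proxy at all assessments where possible, in both arms.
2. Where local session allocation allows, choose a proxy who does not lead that participant's individual IMR sessions.
3. At each assessment, record whether the proxy is IMR-trained and whether they led any of that participant's individual or group sessions. Report the shares by arm.
4. Repeat the proxy analyses without ratings by proxies who led that participant's individual sessions, if enough active-arm ratings remain. Interpret the proxy results with the recorded overlap in view.

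Cost: a few sentences, a short addition to the proxy form and one conditional sensitivity analysis, with no extra staff. Some proxies may know the participant slightly less well. Some named proxies will go unused, because consent follows randomisation. Sessions will need some scheduling around the proxy, on wards where the plan already expects occasional staff shortages.

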#### Process related measures

2.3.6

1.Implementation and normalization of the treatment method

To assess the implementation of IMR and the experiences of staff working with IMR, the S-NoMAD [32] will be used. This will be completed during three time-points, before the start of the intervention (in conjunction with staff-training), three months after treatment commencement and twelve months after treatment commencement. S-NoMAD is a questionnaire designed around the theoretical framework and constructs stipulated within Normalization Process Theory (NPT). NPT is a mid-level sociological theory concerned with explaining implementation processes within the health-care sector [13]. S-NoMAD is a Swedish version of the original British version of NoMAD [33,34], that has been translated to Swedish and validated in samples of Swedish health care workers [32].

Within NPT, implementation processes are conceptualized as dependent on four different generative mechanisms, Coherence, Cognitive Participation, Collective Action and Reflexive Monitoring [13].

S-NoMAD is intended to measure the extent to which health-care personnel engage in actions of these four types. Thus, the questionnaire generates scores on four indexes of these actions. The S-NoMAD questionnaire is divided into three section, A, B and C. In addition to a few items collecting background information about the respondents’ roles within the organizational context (Section A), the questionnaire contains 3 general (Section B) and 20 specific (Section C) questions on the intervention in question. Items on Section B are answered on a 10-point scale, whilst items on Section C are answered on a 5-point scale [32]. As stipulated by the creators of the instrument, we have made certain adaptions to item wording to fit the way we use the S-NoMAD. Mainly these consist of adding the name of the intervention studied, but also include temporal aspects based upon the time point when an assessment is made (i.e. if an assessment is made before or after the IMR intervention has been initiated). With the purpose of generating more in-depth qualitative data on the implementation process, we will also conduct two follow-up interviews with staff in conjunction with the two latter assessment points when S-NoMAD is answered. These interviews will be based on the questions asked in S-NoMAD, with the purpose of giving an opportunity for interviewees to more freely expand upon their reasoning. The interviews will be conducted in a semi-structured manner. A member of the research team will conduct these interviews.2.Quality of treatment delivered

As previously mentioned, the aim is to achieve treatment fidelity by training staff and providing access to weekly supervision. To assess how well treatment fidelity is achieved, audio recordings of IMR session will be made. We plan to record two sessions each from the wards participating in the active treatment conditions. These audio recordings will then be scored for treatment fidelity by the research team. Scoring will be based on the instrument Illness Management and Recovery Treatment Integrity Scale (IT-IS) [17]. This is a rating scale specifically designed to assess the quality of the delivery of the IMR-intervention. The scale is focused on the fidelity to the treatment manual and the strategies specified within. IT-IS is designed to be used by an IMR-proficient supervisor or expert, who, observing a session or material from a session, assesses treatment quality by rating the observed material on 16 items (13 mandatory, 3 optional items) graded on a five point scale. The audio recordings are planned to take place approximately three and five months into treatment.3.Participants’ satisfaction with IMR

To assess the satisfaction with IMR amongst participants in the active group, they will be asked to complete the Client Satisfaction Questionnaire-8 [35] during outcome assessment post-treatment. This is a questionnaire intended to measure clients’ satisfaction with eight items scored on a scale ranging from 1 to 4. Previous studies using the instrument have demonstrated high internal reliability, good construct validity and that the items on the scale load on a single satisfaction factor [36,37].

### Data analysis plan

2.4

Comparisons of primary outcome measures between the two conditions will be made on an intention to treat (ITT) basis. Linear mixed modeling (LMM) will be used to assess main effects of time, treatment and time by treatment interactions. A model based on observations nested within subjects, subjects nested within units and units within forensic settings will be evaluated. Models will be compared according to relevant indices of fit, such as AIC, BIC and Log-Likelihood. To test for group differences, post hoc-independent *t*-test will be performed at all time-points. Effect sizes will be expressed in Cohen's d.

In answering the second primary research objective stated above, pertaining to the influence (or non-influence) of potential moderating factors on treatment outcomes, multiple linear regression will be used as an analysis tool.

In regards to the secondary research objective, exploring the experiences of staff administering IMR, a mixed methods approach will be employed. In analyzing quantitative data from the S-NoMAD and change and stability over time on the four indexes of this instrument, linear mixed models will be employed. In analyzing data from the semi-structured interviews with staff, a qualitative approach will be employed.

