### Design

2.2

The project will be conducted with a cluster randomized study design. Each participating forensic mental health in-patient facility will nominate an even number of wards (i.e. clusters of patients), which will then be randomized to either the active (IMR) or control condition (treatment as usual). Randomization of clusters to condition will be matched, in the sense that each participating in-patient facility will have the same number of clusters within the two conditions (e.g. if four wards take part in the study at one facility, two wards will be randomized to each condition). Recruitment of new participating clusters of patients will take place continually until the desired sample size is reached. Assessments of patient outcome measures take place during four different time-points including baseline measurements.

In addition to the patient focused research, the study also aims to explore how staff implementing IMR experience working with the treatment method. This will be done in a mixed-methods fashion, based on the theoretical framework stipulated in Normalization Process Theory [[13], [42]]. Staff working at wards where IMR is implemented will be asked to complete a questionnaire pertaining to aspects of working with the intervention and queried about the same topic in more in-depth qualitative interviews. Data collection from staff will take place at three time-points during the study.

More details on the specifics of data collection is described below, under the heading “Measurement methods”.

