Prior to randomization of a ward to a specific condition, the patients to subsequently be approached for participation in the study will be identified in cooperation with the clinical team according to the inclusion and exclusion criteria delineated below. After randomization patients fulfilling inclusion criteria at these wards will then be informed about the study and asked for written consent regarding their participation. Recruitment of patients at each ward unit will take place during a time limited window of approximately 3–4 weeks after randomization of the ward unit, before IMR treatment start at wards randomized to the active condition. Given the aforementioned lack of evidence-based interventions in forensic mental health care, we would consider even small effect sizes to be of relevance. With that in mind, we would have preferred a larger sample size to have a sufficiently high probability of discovering such effects. A power calculation conducted in R version 4.1.2. indicated that a total of 228 patients (19 in each cluster) would be needed to achieve 80% power to detect a true effect size of .4, if a small intercluster correlation was presumed. However, it should be noted that some studies of the treatment outcome of IMR have reported substantially higher effect sizes than 0.4 [[16], [40]].

However, the selection of our planned sample size has been made based on a trade-off between a desire for statistical power and pragmatic considerations of what is feasible in a situation of limited time and resources. Furthermore, our study can hopefully be a part of data underlying future meta-analytic studies of the efficacy of treatments within the forensic inpatient context.

In addition to patients participating in the study, staff administering IMR-treatment to patients will also be recruited as participants to the study. These staff participants will answer questions pertaining to their experiences of implementing the intervention. Staff participants will only be recruited from the wards where IMR is implemented. Recruitment of staff participants will take place after the end of staff training prior to treatment commencement. The specific composition of this sample is dependent upon the organization of the wards participating in the study, but it is expected that this will mainly consist of nurses and auxiliary staff. More in-depth inclusion and exclusion criteria both for patient and staff participants are defined below.

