		**Timepoint**			
		**Baseline (pre-treatment)**	**During treatment**	**Treatment completion**	**Post-treatment follow up**
**Outcome measures**	WHODAS	X		X*	X
	IMRs	X	X	X	X
	ASHS	X	X	X	X
	HoNOS-S	X		X*	X
**Process measures**	IT-IS		X		
	NoMAD	X	X		X

**IMRs** = Illness management and recovery scale, **ASHS** = Adult State Hope Scale, **WHODAS**= World Health Organization Disability Assessment Schedule, **HoNOS-S**= Health of Nation Outcome Scale-Secure, **IT-IS**= IMR Treatment Integrity Scale, **NoMAD**=Normalization Process Theory Measure. **IMRs** and **WHODAS** include both client and clinician rated versions of these scales. Post-treatment follow up is planned at three months after treatment completion. Time points for measurement during treatment differs between outcome measures and process measures. * = Denotes a primary outcome measure.

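### Both primary outcomes are scores at treatment completion, but the mixed model is set out as main effects and an interaction, with no baseline-adjusted contrast at completion named as primary

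*Protocol article*

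**What the plan says.** Section 2.3.5 (Outcome measures) ties each primary outcome to one occasion. For disability: "The interview administered WHODAS 2.0 at treatment completion is one of the studies two primary outcome measures". For mental health and security problems: "The HoNOS-S administered at treatment completion is the second primary outcome measure in the study". Table 1 agrees. The asterisk, explained as "Denotes a primary outcome measure", stands only in the treatment-completion column. The table also shows that these two scales are measured three times: at baseline, completion and the three-month follow-up.

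Section 2.4 (Data analysis plan) describes the primary analysis as follows: "Linear mixed modeling (LMM) will be used to assess main effects of time, treatment and time by treatment interactions". It adds the nesting: "A model based on observations nested within subjects, subjects nested within units and units within forensic settings will be evaluated". For group differences it says that "post hoc-independent *t*-test will be performed at all time-points".

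Baseline is counted among the outcome occasions in section 2.2 (Design): "Assessments of patient outcome measures take place during four different time-points including baseline measurements". The article does not mention the baseline score as a covariate in the outcome model.

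**The concern.** The endpoint is one occasion, while the model is described by effects that span occasions. Take the effects in turn:

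- **Time.** This says nothing about IMR against TAU.
- **Treatment main effect.** Averaged over baseline, completion and follow-up, it includes an occasion at which treatment cannot yet have acted. If the model is coded with baseline as the reference occasion, the term is simply the baseline difference between arms.
- **Overall time-by-treatment interaction.** This tests completion and follow-up together. Its completion component compares change from baseline.
- **Post hoc t-test at completion.** This is aimed at the right occasion, but it is labelled post hoc, is repeated at every occasion including baseline, and uses neither the ward nor the baseline score.

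The reader therefore has several candidate answers to the first objective for each scale and is not told which one decides. The trial is also acknowledged to be underpowered (80 patients planned against 228 calculated), and the baseline scores that could improve precision are already being collected.

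**Working it through.** **Inputs from the article.** 12 wards, 6 per arm; 80 patients, 40 per arm, so m = 80/12 = 6.67 per ward; effect size 0.4; three occasions for each primary scale.

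**Assumptions (not in the article).** Two-sided alpha 0.05; SD 1; no dropout; equal correlation r between occasions; r = 0.5 to 0.7; ICC 0.01 to 0.05 (the article says only that it is small); true effect 0 at baseline and d at completion and follow-up.

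**Step 1: the article's own figure.** It states that "a total of 228 patients (19 in each cluster) would be needed to achieve 80% power to detect a true effect size of .4". With 114 per arm, 19 per ward and ICC 0.0075, the design effect is 1 + 18 × 0.0075 = 1.135, z = 0.4/√(2 × 1.135/114) = 2.83, and power is Φ(2.83 − 1.96) = 80.9%. At ICC 0.01 it is 79.4%. The figure of 228 is thus reproduced by an unadjusted comparison at a single occasion, under a normal approximation. With t on 10 ward degrees of freedom, power at 228 would be 72% and 71%. The figure is not in dispute here.

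**Step 2: expected effect and variance factor of each candidate.**

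| Candidate | Expected effect | Variance factor v |
|---|---|---|
| Treatment main effect averaged over 3 occasions | (0 + d + d)/3 = 2d/3 | (1 + 2r)/3 |
| Unadjusted difference at completion | d | 1 |
| Change from baseline to completion | d | 2(1 − r) |
| Baseline-adjusted difference at completion | d | 1 − r² |

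The adjusted-to-change variance ratio is (1 − r²)/(2(1 − r)) = (1 + r)/2, which is 0.75, 0.80 and 0.85 at r = 0.5, 0.6 and 0.7. The adjusted-to-unadjusted ratio is 1 − r², which is 0.64 at r = 0.6.

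**Step 3: power at the planned size, d = 0.4.** The noncentrality is effect/√(2 × v × DE/40), referred to t with 10 df, where DE = 1 + 5.67 × ICC, that is 1.057 at ICC 0.01 and 1.283 at ICC 0.05. This form assumes that the ward component has the same correlation over time as the patient component.

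| ICC | r | Averaged main effect | Unadjusted | Change | Adjusted | Adjusted minus change |
|---|---|---|---|---|---|---|
| 0.01 | 0.5 | 25.1% | 35.0% | 35.0% | 44.3% | 9.3 |
| 0.01 | 0.6 | 23.3% | 35.0% | 42.0% | 50.2% | 8.2 |
| 0.01 | 0.7 | 21.7% | 35.0% | 52.8% | 59.5% | 6.7 |
| 0.05 | 0.5 | 21.5% | 29.8% | 29.8% | 37.8% | 8.0 |
| 0.05 | 0.6 | 20.0% | 29.8% | 35.8% | 43.0% | 7.2 |
| 0.05 | 0.7 | 18.7% | 29.8% | 45.3% | 51.5% | 6.2 |

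Simulated trials over the same range of r and ICC, analysed by ward means with 10 df, give 17-25% (averaged main effect), 28-35% (unadjusted), 31-57% (change) and 39-62% (adjusted). The adjusted contrast ranked first in every scenario.

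**Step 4: where the gain shrinks.** Suppose ward differences are wholly stable over time. Change then removes them, while adjustment with the within-ward slope r leaves ICC × (1 − r)². At r = 0.6 the variances of a ward mean are:

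- Change: (1 − ICC) × 0.8/6.67
- Adjusted: (1 − ICC) × 0.64/6.67 + ICC × 0.16

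At ICC 0.05 these are 0.114 and 0.099, so the 20% saving falls to 13%. At ICC 0.10 they are 0.108 and 0.102, a saving of 5%. At ICC 0.20 they are 0.096 and 0.109, and adjustment is 13% worse.

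High r also narrows the gap. At r = 0.8, ICC 0 and a normal approximation, change has 81% and adjusted 85%. The joint 2-df interaction has 84% if the effect is fully maintained at follow-up and 72% if it is halved.

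**The case against.** The other side has a good case. A longitudinal mixed model with a time-by-treatment term is standard and valid, and a condensed article often leaves coding, covariates and the deciding contrast to an analysis plan. Four stronger readings are tempting, and the article does not support them:

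- **That arms are never compared at completion.** They are. The post hoc t-tests cover all occasions, and with time categorical the interaction contains a completion component. What is lacking is a designated model-based contrast.
- **That the averaged treatment main effect decides the trial.** The article never says so, and in such a model the interaction usually does. The low power of the main effect is a reason not to use it as the test. It does not measure what this trial will lose.
- **That baseline is stated to be an outcome in the model.** This is an inference. It is well supported by baseline being listed among the occasions, time being a factor and no baseline covariate being mentioned, but the model specification is not given.
- **That baseline adjustment always beats change.** Step 4 shows that it need not. Patients also consent after their ward is randomized, so equal expected baselines are not assured; the two approaches then rest on different assumptions, and neither is uniformly right.

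What stands against the plan is that this is not mere silence. The article states an endpoint and states a list of tests, and the two do not match. An unseen analysis plan might resolve this, but the published text would still need to agree with it.

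**Conclusion.** The point holds in a limited form. The endpoint is the score at completion, and the plan names no model contrast there as decisive; the only test aimed at that occasion ignores ward and baseline. This mismatch does not depend on any assumed correlation.

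The efficiency part does depend on assumptions. For d = 0.4 with 12 wards and 80 patients, r of 0.5 to 0.7 and ICC of 0.01 to 0.05, the baseline-adjusted contrast has about 39-62% power, against 31-57% for change and 28-35% for the unadjusted comparison. Within a given scenario the gain over change is about 4 to 9 points. That is worth having at almost no cost, but it does not rescue the trial's power. A clarification should be made, but the planned model is not invalid.

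**What to change.** For each primary scale, name one primary test: the IMR-TAU contrast at treatment completion from the mixed model of post-baseline scores, with the patient's own baseline score as covariate and terms for treatment, occasion, treatment-by-occasion, facility and ward. Make the contrast at the three-month follow-up secondary. State that the time and treatment main effects and the unadjusted t-tests are not tests of effectiveness.

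Because consent follows ward randomization, entering baseline as a covariate is safer than a model that forces the arms to share one baseline mean.

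The cost is a change of analysis wording, with no new data. There is one small downside: patients with no post-baseline score drop out of this model, which matters for the stated intention-to-treat basis. Report the model with baseline as an occasion as a sensitivity analysis.
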